## **2.2. TB Digital Adherence Technologies: evidence in literature**

DOT-dependent treatment management alone has shown to be insufficient to ensure medication adherence and treatment outcomes. Understanding this challenge, the global scientific community has invented Digital Adherence Technologies (DATs) that has transformed DOT to SAT. Such technologies, in general, have been shown to improve TB treatment outcomes and substantially save costs, while available data are yet limited for better conclusions of their effectiveness in different countries and settings. Assessing the TB DATs landscape, and understanding the barriers of non-adherence in its End TB Strategy, the WHO has endorsed in 2017 three DATs: short message service/mobile phone texting (SMS), Medication Event Reminder Monitor (MERM), and video-supported Directly Observed Therapy (VDOT). The SMS involves sending a standardized and understandable text message to the TB patient regularly to remind and motivate them to take the prescribed medications. MERM involves the use of an electronic pillbox consisting of an automated pill

container that emits audible and visual alerts to remind patients to take medication and transmits a signal to healthcare providers either when the box is opened or when it remains unopened for a given time and remotely monitor adherence. MEM pillboxes were in use several decades ago to monitor the usage of pill containers of different medications. MERM sleeves (99DOTS prototype) have an additional component that each medication blister is wrapped in 99DOTS envelopes to send to providers a hidden signal unrecognized by the patient. VDOT involves video communication between patients and healthcare providers, where providers watch patients take their medication, live or self-recorded, and provide advice and support. VDOT is mediated primarily through internet-enabled smartphones, and internet access is a critical component.

There have been limited studies conducted on DATs. For available studies, effectiveness at different resource-limited countries has been a subject of research and controversy. Table 1 summarizes the findings of recent studies conducted on the three DATs.

**Table 1:** summary of existing literature on TB digital adherence technologies

| Reference            | Country     | Design              | Outcome measure                | Finding                      |
|----------------------|-------------|---------------------|--------------------------------|------------------------------|
| SMS           |             |                     |                                |                              |
| Bediang et al 2018   | Cameroon    | RCT: SMS vs DOT     | Treatment success              | No significant difference    |
| Fang et al 2017      | China       | RCT: SMS vs DOT     | Treatment completion rate      | High                         |
| Mohammed et al 2016  | Pakistan    | RCT: SMS vs DOT     | Treatment success              | No significant difference    |
| Liu et al 2015       | China       | RCT: 4 arms         | Pill count, adherence          | No significant improvement   |
| Iribarren et al 2013 | Argentina   | Cross-sectional     | feasibility and acceptability  | acceptable and feasible      |
| MERM          |             |                     |                                |                              |
| Onwubiko et al 2019  | USA         | RCT: MERM vs DOT    | Treatment completion           | Low                          |
| Park et al 2019      | Morocco     | RCT: MERM vs DOT    | Treatment success              | High                         |
| Liu et al 2017       | China       | Multi-method        | User performance, satisfaction | High                         |
| Broomhead et al 2012 | USA         | Cross-sectional     | Treatment outcome, cost        | High, lower cost per patient |
| Thakkar et al 2019   | India       | Cohort, 99DOTS used | Treatment adherence            | High                         |
| VDOT          |             |                     |                                |                              |
| Lam et al 2018       | USA         | RCT: VDOT vs DOT    | Treatment completion           | High                         |
| Garfein et al 2018   | USA         | RCT: VDOT vs DOT    | Adherence, cost                | High, lower cost             |
| Nguyen et al 2017    | Vietnam     | Prospective cohort  | Treatment adherence            | High                         |
| Chuck et al 2016     | USA         | RCT: VDOT vs DOT    | Treatment outcomes             | No significant difference    |
| Garfein et al 2015   | USA, Mexico | Single-arm trial    | Treatment adherence            | High in both settings        |

RCT: randomized controlled trial; USA: United States of America

Considering the low impact of SMS on TB treatment adherence and the high investment and technology need of VDOT, this study plans to focus on MERM (electronic pillbox) intervention. It is the most

commonly used device to promote medication adherence for different diseases. With a pillbox, patients can self-manage their medications, identify whether they have taken the dose or not, and minimizes the rate of medication errors. Previous studies found that people who used a pillbox had better treatment adherence. This device is associated with improvements in medication adherence and, subsequently, with better health. MERM electronic pillbox has an additional feature of reminding patients to take their drugs with visual and audio alerts, providing information about treatment adherence. However, there are concerning limitations with MERM, such as battery replacement or wireless signaling for sending and receiving messages, that are relevant to developing countries like Ethiopia and need further exploration.

### 3. CONCEPTUAL FRAMEWORK

Figure 4 illustrates the conceptual framework that provides the theoretical basis of the study and demonstrates potential outcome and long-term impact on it on End TB if certain conditions are fulfilled.

[figure not shown]

**Figure 4:**Conceptual framework of the study

This framework applies the functional linkage between TB innovation and the End TB strategy as a common ground that any TB intervention should have an ultimate goal realizing the End TB strategy, with patient rights “practically” guaranteed. This can be traced to the origins of “empowerment theory” - connecting individual-welling with the larger political and social environments through which individuals and groups gain greater control over their lives, acquire rights, and reduce marginalization.

The framework is guided by WHO's recent (2017) handbook for the use of digital technologies to support tuberculosis medication adherence and the WHO's 2016 guideline for monitoring and evaluating digital health interventions. The success of the MERM pillbox as a medication adherence device relies on its efficacy, usability, cost-effectiveness, acceptability, behavioral and social determinants of patients and the broader digital health ecosystem of the implementing country. If these fairly benefit the system, it is likely that TB treatment will succeed, the patient's quality of life will be improved, disease transmission and nosocomial transmission will cease, and will reduce mortality and morbidity due to the disease, and ultimately the End TB strategy will be met.

#### **4. HYPOTHESIS**

- The use of a digital medication event reminder and monitor device-observed self-administered therapy provides a non-inferior medication adherence and treatment outcomes for patients with TB compared with the standard in-person DOT in Ethiopia, one of the low-income countries with the highest burden of TB

## **5. OBJECTIVES**

### **5.1. Primary objectives**

#### **5.1.1. Treatment adherence**

To assess whether a digital medication event reminder monitor (MERM) device-observed self-administered therapy improves adherence in patients with TB compared with the standard DOT.

#### **5.1.2. Treatment outcomes**

To assess whether MERM-observed self-administered therapy improves treatment outcomes in patients with TB compared with the standard DOT.

### **5.2. Secondary objectives**

#### **5.2.1. HRQoL and catastrophic cost**

To evaluate if MERM-observed therapy provides higher HRQoL and lower catastrophic costs compared to the standard DOT

#### **5.2.2. Usability and treatment satisfaction**

To evaluate the patient-reported usability and treatment satisfaction with MERM-observed self-administered TB therapy compared with the standard in-person DOT

## **6. OUTCOME MEASURES**

### **6.1. Primary outcome**

#### **6.1.1. Level of adherence**

- Individual-level percentage adherence over the two-month intensive phase measured by adherence records compiled from MERM device vs. DOT records.

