
The Ethiopian national TB program adheres to the WHO End TB strategy for its TB functions. The national comprehensive TB guideline revised in 2016 standardizes the provision of one first-line anti-TB treatment regimen for both new and previously treated TB patients. The treatment is administered in two phases (Figure 3). The initial (intensive) phase consists of a fixed-dose combination of four drugs [(isoniazid (H), rifampicin (R), pyrazinamide (Z) and ethambutol (E), with 75/150/400/275 mg strength] to be taken for the first eight weeks for new cases. The second (continuation) phase consists of a fixed-dose combination (RH, with 75/150 mg strength) to be taken for four months for new cases, which may be extended to 10 months if the disease involves the central nervous system, bones or osteoarticular spaces. Management of treatment is entirely driven by DOT implementation principles and modalities.

[figure not shown]

 Bacteriologically confirmed TB patients include those diagnosed by a positive result on AFB microscopy, Xpert MTB/RIF Assay or culture;  DST may be performed from one sputum sample using Xpert MTB/RIF, LPA or conventional DST based on availability. Information on rifampicin may be enough to decide on Next Action.  if DST result shows resistance to INH but susceptible to Rifampicin; treat with RHZE for 9 months.

**Figure 3.** Flow Chart for Sputum AFB monitoring for bacteriologically confirmed PTB Patients

In Ethiopia, there have been no alternative TB treatment strategies to DOT to address patient-specific adherence barriers or challenges. This would have a significant impact on the End TB indicator of “Zero TB-affected families facing catastrophic costs due to TB by 2035”. Besides, Multidrug-resistant TB (MDR-TB) remains a serious issue in the country, with a high burden and transmission potential. Such evidence discloses the difficulty of Ethiopia in meeting the overall End TB strategy targets by 2035 unless significant investment is made to shape the current DOT strategy into a more advanced, technology-led, patient-centered strategy that could be responsive to individual patient preferences, needs and values.

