The device has a medication intake event in an electronic record that is created when a patient opens the device to take his or her medication. It consists of a date-and-time stamp. The dispenser provides an electronic heartbeat to a central management system whenever medication is taken, and this also indicates that the device was functioning during that period.

The alarm period is 30 minutes in length and consists of three-alarm cycles. The alarm cycles are 10 minutes each and made up of two parts. These alarms apply regardless of the type of reminder selected. The first five minutes of the alarm cycle is the active alarm. During the active alarm, the buzzer will sound, and the green LED will flash in the following sequence: short, short, long. The yellow LED will flash if the “Refill Alarm” is configured and the date is less than or equal to the current date. The second five minutes of the alarm cycle is the passive alarm. During the passive alarm, the buzzer will not sound, and the green LED will not flash. The yellow LED will continue to flash if the “Refill Alarm” is configured and the date less than or equal to today. Opening the container will cancel the active alarm if it is opened within four hours before the scheduled alarm or if it is opened during the alarm period.

The evriMED500 makes use of two AA batteries which should last for more than 12 months. Regarding storage capacity, it can store more than 12000 records/events. The evriMED PC Application is configured by the evriMED PC Application and it allows a direct connection to the evriMED device via a USB cable. Specification of the evriMED500 is summarized in table 2.

**Table 2:** Summary of evriMED500 specification

| Item                                                     | Specification                                                           |
|----------------------------------------------------------|-------------------------------------------------------------------------|
| Data Storage                                             | 12000 records                                                           |
| Battery Life (Alkaline)                                  | 12+ months                                                              |
| Power requirements                                       | Two AA batteries                                                        |

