### **8.6. Interventions**

Participants in the intervention arm will receive a 15-days TB medication supply (HRZE fixed-dose combination therapy of 15 doses) in an electronic pillbox device (evriMed500 digital medication monitoring and reminder device manufactured by Wisepill Technologies, South Africa) to self-administer. Providers will collect baseline data, including demographic, socioeconomic, behavioral, and social factors using the study's baseline questionnaire. Based on the baseline data, participants will be clustered into four behavioral determinants (use cigarettes, alcohol, Khat - a psychostimulant plant, and cocaine/marijuana) and three social determinants (homeless, unemployed, and illiterate) as appropriate for the purpose of analysis. Participants in this arm will return every 15 days, where the provider will count any remaining tablets in the pillbox, download the pill-taking data from the Wisepill device, evaluate the functionality of the device and troubleshoot as needed, and perform the urine

isoniazid test. The level of adherence in their intensive phase of treatment will be calculated using the medication possession ratio (MPR). Any participant who misses more than five tablets in any 15- day refills will be reassigned to daily DOT throughout the remaining days of the intensive phase. Participants in the intervention arm can consult the healthcare provider in cases of medical illness or any adverse events outside of a scheduled visit before the next appointment. The phone number of the healthcare provider following their TB condition will be written at the backside of their appointment cards. The phone call strategy aims to maintain the DOT advantage for the intervention arm.

Participants in the control arm will get their treatment as per the standard practice of DOT, where participants will visit the healthcare facility each business day throughout the two months intensive phase to swallow their daily dose of HRZE with direct observation by the healthcare provider. Additionally, they will be given pills for the weekend to take them at home. The provider will collect baseline data, conduct a urine isoniazid test every 15-days, and cluster participants into behavioral and social determinants as applicable for participants in the intervention arm. For this arm, the management of participants who interrupt treatment will follow the national TB treatment guidelines.

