For both arms, the providers will collect baseline data, including demographic, socioeconomic, behavioral, and social determinants social using the study's baseline questionnaire. For participants in the intervention arm, the providers will orient participants in the intervention arm as they enroll about how to use the evriMED500 device. The orientation time will depend on the efficiency of the participants to fully acquire and demonstrate the necessary skills. Providers will then dispense a 15-days TB medication supply (HRZE fixed-dose combination therapy of 15 doses) to participants within the evriMed500 device for self-administration. Providers will collect sputum specimens from participants; write their cell phone numbers at the backside of participants' appointment cards to communicate in cases of medical illness or any adverse events before the next appointment, and inform them to return every 15 days. When participants returned, the providers will count any remaining tablets in the pillbox, download the pill-taking data from the evriMED device, check functionality of the device, and conduct a urine isoniazid test. The providers will fill out the study's adherence follow-up form to capture information if the drugs are taken every day, and if not, the reasons for non-adherence. The providers will then evaluate the level of adherence based on the preset criteria, and refill a 15-day TB medication supply in the same pillbox as appropriate. The providers will collect sputum specimens from participants at the end of the intensive phase.

For the control arm, providers will handle participants according to the standard DOT procedure, where participants will visit the healthcare facility each business day in the intensive phase to swallow their daily dose of HRZE with direct observation by the provider. The providers will fill out a similar adherence follow-up form for the control arm. Additionally, if a participant in the control arm requests medications

for self-administration, the provider will collect information about the date requested and for how many days requested on the follow-up form.

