## **9. STATISTICAL ANALYSIS**

Descriptive summary measures will be used to report participant characteristics. Chi-square tests will be used to evaluate potential associations among categorical variables. To compare the level of adherence between study arms and among variables, independent t-tests will be done on log-

transformed adherence percentage of the expected 60 days. Effects of the arms and other adherence variables will be estimated using a geometric mean (GM) with geometric standard deviation (GSD) and mean ratios (MR) with 95% confidence intervals (CI). Log binomial regression will be conducted to identify risk factors of at least one negative isoniazid urine test and self-reported adherence of participants. Effects will be measured using adjusted relative risk (ARR) with 95%CI. A general linear model will be done on log-transformed adherence percentage to identify the effects of variables on participants' level of adherence. Effects will be measured using an adjusted mean ratio (AMR) with 95% CI.

Descriptive statistics including frequency and percentage will be used to describe the health state of the study participants. Multiple bar charts with cross-tabulation will be used to illustrate distributions of health states by study arms. Chi-square and Fisher's exact tests will be employed to compare the five EQ-5D-5L health domains by study arms. Kolmogorov–Smirnov, Shapiro–Wilk tests, and median values with interquartile range (IQR) will be used to summarize EQ-5D-5L index value/utility. Nonparametric Mann–Whitney U test will be employed to compare the difference in EQ-5D-5L index value/utility among study arms. A log-binomial model will be used to identify risk factors for lower HRQoL, which is having at least one health problem.

The overall TB treatment cost will be estimated by considering costs related to anti-TB drug pick-up, guardian costs, and coping costs over the two-month intensive phase. The proportion of study participants who faced catastrophic costs at a cut-off point of 20% will be estimated. A cross-tabulation will be employed to evaluate the distribution of catastrophic cost over the study arms and chi-square test will be used to test the association between catastrophic cost and study arms.

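### Primary adherence uses device openings on every day in one arm and DOT records in the other, where about 29% of the 60 days are unobserved; the unstated scoring of those days can move the control mean by more than the 20-point margin

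*Protocol*

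**What the plan says.** - **Measure.** Section 6.1.1 defines the first primary outcome as individual percentage adherence over the intensive phase, "measured by adherence records compiled from MERM device vs. DOT records".
- **Device record.** In Section 8.1 an intake event is a date- and time-stamped entry "created when a patient opens the device to take his or her medication". It can arise on any day of the week.
- **DOT record.** In Section 8.6 control "participants will visit the healthcare facility each business day throughout the two months intensive phase". On weekends there is no observation: "they will be given pills for the weekend to take them at home".
- **Further unobserved control doses.** Section 8.7 provides that "if a participant in the control arm requests medications" to take alone, the provider notes the date and the number of days. Approved self-administered doses get a separate secondary analysis.
- **Denominator.** Section 9 tests the log-"transformed adherence percentage of the expected 60 days", with no distinction by arm.
- **A second definition.** Section 8.6, describing the intervention arm, says its adherence level is calculated as a medication possession ratio. The same section moves intervention participants who pass a missed-tablet threshold to daily DOT for the rest of the phase.
- **Planning values.** Section 8.5.1.5 uses a mean of 79% in both arms, SD 36%, a margin of 20%, one-sided 2.5%, power 80% and 10% attrition, giving 57 per arm.

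**The concern.** Both arms share a 60-day denominator, but they do not share the days on which a dose can be seen to be taken or missed. A MERM participant who skips a Saturday leaves a gap in the device log. A control participant who skips the same Saturday leaves nothing, because nobody was watching.

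The protocol does not say whether such a control day counts as taken, missed or excluded. With 60 days kept in both arms, scoring all of these days as taken or all as missed is biased, in opposite directions. In a non-inferiority trial with one adherence margin, part of the primary contrast would then reflect the recording rule and not the patients. The possession-ratio wording adds a third possible numerator for the intervention arm.

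**Working it through.** **Step 1. Reproduce the plan's sample size.** With margin 20, SD 36, true difference 0, one-sided 2.5% and power 80%:

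n = 2 × 36² × (1.960 + 0.842)² / 20² = 50.9, so 51 per arm. Then 51 / 0.9 = 56.7, so 57.

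This matches the protocol and shows that the margin was used as 20 absolute percentage points. With 51 evaluable per arm, SE = 36 × √(2/51) = 7.13.

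**Step 2. Unobserved control days.** Assume a Saturday–Sunday weekend and ignore public holidays. The weekend share is w = 2/7, so 60 × 2/7 = 17.1 days (28.6%), leaving 42.9 observable days. Depending on the start day the count is 16 to 18 days (26.7% to 30.0%). Approved take-home doses on business days would add to this; the protocol gives no number for them.

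**Step 3. Size of the artefact.** Let true adherence be a in both arms, the same on weekdays and weekends, and let r be the rate at which control weekend doses are recorded as taken. MERM records a. Control records (1 − w)a + wr. The artefact, MERM minus control, is w(a − r). At a = 79%:

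| Weekend scoring in control | r | Control recorded | MERM minus control |
|---|---|---|---|
| Not taken (observed doses only) | 0% | 0.714 × 79 = 56.4% | +22.6 (21.1 to 23.7 for 16 to 18 days) |
| Credited when the pack is collected, collection at 79% | 79% | 56.4 + 0.286 × 79 = 79% | 0 |
| Every weekend dose credited | 100% | 56.4 + 28.6 = 85.0% | −6.0 (−5.6 to −6.3) |

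From r = 0% to r = 100% the control mean moves by 28.6 points (26.7 to 30.0), more than the margin. The artefact itself exceeds 20 points only if doses are scored not taken and true adherence is above 20 / 0.286 = 70%.

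**Step 4. Effect on the decision.** P(non-inferior) = Φ((d + 20) / 7.13 − 1.96), where d is the expected recorded difference, MERM minus control, and SD is held at 36.

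- No artefact, arms truly equal: d = 0, probability 0.80, as planned.
- Every weekend dose credited, arms truly equal: d = −6.0, probability 0.50.
- Observed doses only, MERM truly at the margin (59% against 79%): d = 59 − 56.4 = +2.6, probability 0.89 instead of 0.025.
- Every weekend dose credited, MERM truly at the margin: d = 59 − 85.0 = −26.0, probability 0.003.

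**Step 5. Log scale.** Sections 8.5.1.5 and 9 put the comparison on log-transformed adherence. At true equality the artefact is then a control/intervention ratio of 56.4/79 = 0.71 (observed only) or 85.0/79 = 1.08 (all credited). It does not disappear.

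**Step 6. Check the observed-only rule against the plan.** That rule caps control at 42.9/60 = 71%. A control mean of 79%, as in Section 8.5.1.5, could not then occur.

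**The case against.** **A reader might infer that the arms differ by more than the margin by design, or that a false non-inferiority claim is nearly assured.** The protocol does not support this. It states no observed-only rule, the 22.6-point gap and the 89% figure need one, and such a rule is incompatible with the 79% planning mean. Weekend pills are supplied as part of control treatment, so they naturally belong among the expected doses. This objection stands, and the observed-only case is kept only as a worst case.

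**Crediting packs need not give 100%.** Someone who misses the visit at which weekend pills are handed out may get no pack. If collection runs at 79% the artefact is zero. This also stands: the bias under crediting is 0 to about 6 points, and it runs against MERM, so it costs power and does not inflate the false-positive rate.

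**Control days are not wholly unmonitored.** A follow-up form similar to the MERM-arm form is completed, take-home requests are logged, and both arms have a urine isoniazid test every 15 days and a self-report. That is fair, but a report on a form is still not the dated electronic event scored on the same days in the other arm. The urine test (four per participant) and the self-report are secondary outcomes and do not correct the primary contrast.

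**The scoring rule belongs in the statistical analysis plan.** That plan is not at hand and may state the rule, so its absence here is not the finding. The record sources, business-day observation, the common 60-day denominator and the possession-ratio wording are all fixed by the protocol, and they create the asymmetry.

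**Eight weeks against 60 days.** Section 2.1 describes the intensive phase as "to be taken for the first eight weeks for new cases", which is 56 days, or 93% of 60. This is background text, and a shorter phase would affect both arms alike, so it cannot explain a difference between them. The two durations should be reconciled, but the point is minor.

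**Conclusion.** The point holds as a defect in the definition of the primary endpoint. The two arms are scored out of the same 60 days with different instruments, and about 28.6% of control days have no observed record. The scoring choice can move the control mean by up to 28.6 points, against a 20-point margin.

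On the reading that fits the planning mean (unobserved doses credited), the bias at equal 79% adherence is 0 to about 6 points against MERM, and power falls from 80% to as low as about 50%. The 22.6-point gap in favour of MERM, with its 89% false non-inferiority rate, is a worst case that conflicts with Section 8.5.1.5 and should not be read as what the protocol prescribes.

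These sizes assume a Saturday–Sunday weekend, equal weekday and weekend adherence, SD 36 under every rule, 51 evaluable per arm, and a normal approximation on the percentage-point scale. Separately, the possession-ratio wording in Section 8.6 contradicts the record sources in Section 6.1.1.

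**What to change.** Define primary adherence on the same days and by the same rule in both arms:

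- **Days:** each participant's scheduled business days in the intensive phase, as both eligible days and denominator.
- **Numerator:** a day counts if there is at least one patient opening (MERM; provider openings at refill excluded) or one observed dose (control, and intervention participants after reassignment to DOT).
- **Approved control take-home doses on business days:** credited as taken in the primary analysis, which is conservative for MERM, and as not taken in a sensitivity analysis.
- **60-day score:** reported as a sensitivity analysis with its weekend rule stated.
- **Text:** remove the possession-ratio wording or reconcile it with Section 6.1.1, and reconcile the eight-week and 60-day descriptions.

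Under this rule the weekend artefact is zero. The change is to the endpoint definition only: device events are already date-stamped, take-home requests are already logged, and no clinical procedure changes.

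The cost is that about 29% of MERM days leave the primary score, so it describes business-day adherence and not the whole phase. It also leaves one difference in place: opening a box is weaker proof of intake than an observed dose. That limitation should be stated with the result.
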